### Outcome measures

All study participants will attend two sessions at the clinical site: at baseline (week 0) and post-intervention (week 10), where a blinded outcome assessor will collect outcome measure data. Participants will be asked to complete a subjective questionnaire set, walking/balance tests, a verticality perception test and a cognitive screen. These will take approximately 1.5 hours, including comfort breaks. Participants’ e-health literacy will only be collected at baseline, while system usability score (SUS) and User Experience Questionnaire (UEQ) will be collected post-intervention among the IG only.

The outcome assessor will be asked to record any incidences of unblinding and detail how this occurred. Due to the nature of this study, we do not foresee circumstances where emergency unblinding of the outcome assessor is required.

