#### Primary outcome measures

Primary outcomes of feasibility, acceptability, usability and safety will be investigated alongside clinical measures of Functional Gait Assessment (FGA) and EuroQol five-dimensional descriptive system (EQ-5D-5L) instrument pre-intervention and post-intervention. The FGA includes 10 tasks that assess dynamic and complex gait (eg, walking with head turns or stopping and turning), with a minimal detectable change (MDC) of 4.2 points in stroke populations and 6 points in vestibular disorders^61^ and minimally clinically important difference (MCID) of 4 points in community-dwelling older adults.^62 63^

Programme effectiveness will be evaluated using quality-adjusted life years (QALYs) measured with the EQ-5D-5L instrument.^64^ The EQ-5D-5L is a standardised, valid and reliable measure of health status for clinical and economic appraisal.^64^ The respondent is asked to rate their health status on five dimensions (mobility, self-care, usual activities, pain/discomfort, anxiety/depression), followed by a self-rated health score from 0 to 100. MCID ranges from 0.03 to 0.52.^65^,^67^

Primary outcomes are as follows:

*Acceptability*: recruitment (percentage of eligible participants enrolled); dropout rates; intervention adherence (percentage of prescribed sessions completed) monitored automatically through the system for TeleRehaB DSS participants and via an exercise diary for control groups.*Safety*: participants will be monitored for adverse event’s via completion of adverse events forms on the system database, during telephone or face-to-face contacts as part of the intervention phase and during follow-up assessments. Falls diaries will be collected weekly from participants during the intervention, and monthly for up to 6 months after completion of the intervention.*Feasibility*: protocol deviation (PD) or study protocol implementation problems (eg, logistical).*Usability*: participants’ experience using the system (perceived benefits, frustrations and recommendations) will be explored via exit interviews for all TeleRehaB DSS group completers. These participants will also complete the SUS^68^ and UEQ^69^ to explore system usability and user experience, respectively.

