### Data management and analysis

#### Statistical analysis

Anonymised data will be entered into a study database. Data integrity will be assessed by taking a random 10% sample of entries following completion of data collection. The rectified database will be saved under a new filename (eg, study database_rectified_date) and all changes made to the database will be logged. All essential trial documentation will be saved on the dashboard except for the consent form which will be saved at each clinical site in paper form. The sponsor will ensure that study documentation is retained in accordance with their local approvals after the conclusion of the trial.

As this is a feasibility study, there is no formal plan for statistical analysis. However, for a future trial, an analysis plan has been developed which will be run in this study to determine its appropriateness. Descriptive statistics will be used to summarise feasibility outcomes of adherence, compliance and dropout rates. Continuous secondary outcome measures will be reported as means with 95% CIs.

Normality of outcome variables will be assessed by visual inspection and appropriate statistical tests. Where assumptions of normality are met, intention-to-treat analyses will be conducted using repeated-measures general linear model analysis of variance to explore between-group and within-group trends, adjusting for clinical site and cohort. Where normality assumptions are not met, non-parametric alternatives will be employed, including Wilcoxon signed-rank tests for within-group comparisons, Mann-Whitney U test for between-group comparisons and Friedman tests for repeated measures where appropriate.

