#### Statistical approach for quality-adjusted life year and cost-effectiveness analysis

A mixed-effects regression model will compare QALYs and costs between groups, adjusting for confounders like age, baseline health and site. Cost-effectiveness will be evaluated against willingness-to-pay thresholds (eg, £20 000–£30 000 per QALY in the UK) to determine if TeleRehaB DSS is a cost-effective alternative to standard care.

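### The between-arm analysis of the before-and-after clinical scales omits the baseline score as a covariate, so its group-by-time term is an unbiased but less precise change-score contrast, and the arm contrast is not named

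*Protocol article*

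**What the plan says.** Under Statistical analysis, the protocol article gives one parametric model for continuous outcomes: "intention-to-treat analyses will be conducted using repeated-measures general linear model analysis of variance to explore between-group and within-group trends, adjusting for clinical site and cohort". Site and cohort are the only adjustments named. If normality fails, rank tests replace the model.

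Under Outcome measures, the scales are collected "at baseline (week 0) and post-intervention (week 10), where a blinded outcome assessor will collect outcome measure data". Under Primary outcome measures, the clinical primaries are "clinical measures of Functional Gait Assessment (FGA) and EuroQol five-dimensional descriptive system (EQ-5D-5L) instrument pre-intervention and post-intervention". Table 2 shows the same pattern for the secondary scales with a pre-intervention value: one value at screening or baseline and one at week 10. The caption of Figure 2 counts the week 3 and week 6 reviews among the assessments, but Table 2 lists no outcome scale at those weeks.

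QALYs have their own section and model: "A mixed-effects regression model will compare QALYs and costs between groups, adjusting for confounders like age, baseline health and site".

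**The concern.** With only two measurement times, the repeated factor must be baseline against week 10. The baseline score is therefore part of the outcome, although it could have been used to explain variation in the week-10 score. Such a model offers two terms that involve arm:

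- **Group-by-time.** This is the difference between arms in mean change. It subtracts the whole baseline value, whereas the best prediction of the week-10 score uses only part of it. The result is extra variance.
- **Between-group main effect.** This is the difference between arms in the average of baseline and week 10. Randomised arms have the same expected baseline, so any treatment effect is diluted by half.

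The article mentions between-group and within-group trends without saying which term is the treatment comparison. The choice matters beyond this trial. The Trial design section says the results are to provide sample size estimates for a future trial. The Statistical analysis section says the plan is being run here to see whether it suits that trial.

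**Working it through.** **Plan's own figure.** The target is 460. Five sites at 60 to 100 each give 300 to 500, which contains 460 (460/5 = 92 per site). No alpha, power, effect size or SD is given, so 460 cannot be derived by formula. Equal intervention and control numbers per site imply about 230 against 230.

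**Inputs.** From the article: two assessments, and adjustment for site and cohort only. Assumed, because the article does not give them: equal SD s before and after, and pre-post correlation rho from 0.3 to 0.9.

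**Formulas** (each variance is multiplied by 1/n1 + 1/n2; δ is the true difference at week 10).

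- Group-by-time (change): estimates δ, variance 2(1−rho)s².
- ANCOVA with baseline as covariate: estimates δ, variance (1−rho²)s².
- Between-group main effect: estimates δ/2, variance ((1+rho)/2)s². Rescaled to δ, this becomes 2(1+rho)s².

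Ratio of change to ANCOVA: 2(1−rho)/[(1−rho)(1+rho)] = 2/(1+rho). Ratio of rescaled main effect to ANCOVA: 2(1+rho)/[(1−rho)(1+rho)] = 2/(1−rho).

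| rho | Change / ANCOVA variance | Standard error ratio | 460 analysed by change is worth, under ANCOVA | 95% CI half-width in SD units, 230 v 230: change, ANCOVA | Rescaled main effect / ANCOVA variance |
|---|---|---|---|---|---|
| 0.3 | 1.54 | 1.240 | 299 | 0.216, 0.174 | 2.86 |
| 0.5 | 1.33 | 1.155 | 345 | 0.183, 0.158 | 4.00 |
| 0.7 | 1.18 | 1.085 | 391 | 0.142, 0.131 | 6.67 |
| 0.8 | 1.11 | 1.054 | 414 | 0.116, 0.110 | 10.0 |
| 0.9 | 1.05 | 1.026 | 437 | 0.082, 0.080 | 20.0 |

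**Unequal variances.** The change variance minus the ANCOVA variance is SD_pre² + SD_post² − 2·rho·SD_pre·SD_post − SD_post²(1−rho²) = (SD_pre − rho·SD_post)². This is never negative, so in large samples ANCOVA is not the less precise of the two.

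**Checks.**

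- In a two-time data set, the group-by-time F equalled t² on change scores (1.5338 both ways). It did so again with site-by-time in the model (1.3262 both ways), so adjusting for site leaves it a change-score contrast.
- In 4,000 simulated trials at each of rho 0.5 and 0.7 (230 v 230, true difference 0.25 SD), change and ANCOVA both averaged 0.248 and 0.252. The main effect averaged 0.125 and 0.126, which is half.
- The simulated variance ratios of change to ANCOVA were 1.34 and 1.18, against 1.33 and 1.18 in theory.

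**The case against.** **The trial is exploratory.** The article says that its sample is not sized for clinical effectiveness and that, as a feasibility study, it has no formal analysis plan. This stands as a limit on importance. It is why the size is given here as variance and interval width, since any power figure would rest on an assumed effect as well as an assumed rho. It does not dispose of the point, because the same model is being tried out for a definitive trial and its estimates are to size that trial.

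**The analysis is not wrong.** This also stands. A reader might infer that the comparison is a raw or biased one. It is neither: site and cohort are adjusted for, and the group-by-time contrast is unbiased under randomisation with valid intervals. What is lost is precision.

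**The halved effect is not stated.** A reader might infer from the reference to between-group trends that the main effect will be reported as the treatment effect. The article names no contrast, and a reference to trends fits group-by-time at least as well. The halving is a conditional risk. A condensed article may leave the contrast to a fuller plan; the model and its adjustment list, however, are stated outright.

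**Baseline is adjusted for elsewhere.** This is true for QALYs and costs, so QALYs derived from EQ-5D-5L fall outside the point. The abstract also mentions mixed-effects models and adjustment for relevant confounders, but the body specifies these only for QALYs and costs. Nothing extends them to FGA or the secondary scales.

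**The model is conditional.** It applies only where normality is accepted, so how many scales it reaches is unknown.

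**Conclusion.** The point holds as a matter of precision and of an unnamed contrast. For FGA, for the EQ-5D-5L score where it is analysed by this model, and for the secondary scales, the stated analysis leaves out a covariate that is already collected.

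With equal variances, the group-by-time contrast has 1.05 to 1.54 times the variance of ANCOVA for rho between 0.9 and 0.3, so its intervals are about 2.6% to 24% wider. The gain from the change is small if pre-post correlation is high and worthwhile if it is moderate. The article gives neither rho nor an SD, so no single figure can be claimed.

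If the between-group main effect were taken as the treatment effect, the estimate would be about half the truth. A later trial sized on it would be about four times too large with the SD unchanged, because required size goes with 1/δ² and 1/(1/2)² = 4. The documents do not show that this reading is intended.

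Importance is moderate: it is a free improvement in an exploratory trial whose estimates feed the next one.

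**What to change.** In the Statistical analysis section, replace the repeated-measures ANOVA for between-arm comparisons with a regression of the week-10 score on arm, with the baseline score of the same measure, clinical site and cohort as covariates. A mixed model that constrains the arms to a common baseline mean would serve equally. Report the arm coefficient with its 95% CI as the between-group estimate. State that the between-subjects main effect of a repeated-measures model is not used as the treatment effect.

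Apply this to FGA, to the EQ-5D-5L score where it is analysed here, and to each secondary scale with a pre-intervention value. The QALY and cost model needs no change on this account. Reporting the observed pre-post correlation and SD of each scale would give the next trial the inputs that are missing here.

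The cost is a few sentences of analysis wording. It needs no new data, visits or participants.

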#### Inclusion criteria

All participants must meet the below criteria for consideration in the study, with additional specific criteria for each disease cohort (table 1).

**Table 1 T1:** TeleRehaB DSS clinical study inclusion criteria

All participants	Age 40–80 years. Community dwelling able to walk 500 m independently or with a stick. HADS depression subscale score <10/21. No significant visual impairment (as self-reported by participants). Willing to comply with study procedures, proposed training and testing regime. Able to understand and consent to the research. Has at least one functional hand for grip function and computer use. Fulfilling all of the criteria from one of the below subgroups
Stroke participants	Individuals with diagnosis of focal ischaemic or haemorrhagic stroke, as confirmed by a clinical letter. Onset >6 months prior to study. MoCA score >23. FGA score <22/30 AND/OR having experienced a fall(s) in the last 12 months. If diagnosed with drop foot, must have a corrective device (AFO, FES etc.) must be in-place for exercise performance.
MCI participants	Individuals with diagnosis of MCI, according to the ICD10 (G31.84),^92^ as confirmed by a clinical letter. FGA <22/30 AND/OR having experienced a fall(s) in the last 12 months.
Vestibular dysfunction participants	Individuals with a diagnosis of a vestibular disorder (peripheral and/or mixed peripheral and central) as confirmed by a clinical letter: Peripheral vestibular disorder in which the balance problem lies in the vestibular/balance system within the inner ear. Mixed vestibular disorder in which the balance problem lies in the vestibular/balance system within the inner ear (peripheral) and involving the nerves or neuronal network in the brain/brainstem responsible for balance (central). Chronic dizziness and/or unsteadiness (>3 months duration) due to a vestibular disorder. DHI score >34 AND/OR FGA score <22/30. MoCA score >23.
Long covid participants	Individuals with laboratory confirmed diagnosis of COVID-19 (>6 months prior to study onset) AND/OR who have been diagnosed with long covid, as confirmed by a clinical letter. Who have chronic dizziness and/or unsteadiness which started after the COVID-19 illness (self-report by the patient; duration >3 months). DHI score >34 AND/OR FGA score <22/30. MoCA score >23.

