## Discussion

This manuscript outlines the TeleRehaB DSS pilot feasibility protocol, a global, multisite RCT spanning clinical sites in the UK, Greece, Germany, Madeira and Thailand. Following a remote 9-week MBR programme delivered to adults at risk of falls due to stroke, MCI, vestibular dysfunction or long covid, the study aims to (1) determine the system’s safety, acceptability and feasibility; (2) assess how QOL, balance function and confidence, cognitive function and well-being compare to standard of care; and (3) provide preliminary data for a definitive RCT.

Preliminary findings from the HOLOBalance project, TeleRehaB DSS’ predecessor, support that a remotely delivered MBR is feasible to implement and acceptable to older adults at risk of falls, with balance and gait outcomes (FGA and Mini-BESTest) exceeding those from the OTAGO programme.^47^ Therefore, we hypothesise that the TeleRehaB DSS, a refined iteration of HOLOBalance, will be feasible to implement and acceptable to adults with stroke, MCI, vestibular dysfunction and long covid, although we do expect to receive disease-specific feedback from these patient cohorts, informing disease-specific refinements required to address each cohort’s needs. For example, patients who had a stroke commonly present with hemiplegia on one side of the upper and/or lower limbs, warranting exercise modifications to address these limitations. We also expect that MCI cohorts may require additional reminders and motivational prompts due to cognitive challenges such as memory. We expect the system to be safe, with minimal adverse events, as demonstrated in HOLOBalance (n=3 adverse events).

Compared with standard of care (OTAGO or Balance Retraining Booklet), we expect to see improved QOL, balance function, balance confidence and well-being in the TeleRehaB DSS intervention arms. HOLOBalance findings support this hypothesis, with FGA and Mini-BESTest findings meeting or approaching the MCID in the intervention group.^47^ This first iteration of the current TeleRehaB DSS demonstrates that provision of supervised remote home treatment for MBR provides notable benefits at reducing falls risks.^47^ Therefore, we expect that a more mature version will result in equal to if not better results following an extended treatment time of 9 weeks with additional exercises, improved instructions and ICT platforms, including hardware and software updates.

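### Within-arm pre/post tests on FGA and DHI reuse the reading that can qualify a participant, so regression to the mean can push their false-positive rate above 5% by an amount the protocol cannot bound

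*Protocol article*

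**What the plan says.** Both branches of the Statistical analysis section look at change within an arm. If normality holds, a repeated-measures ANOVA is used "to explore between-group and within-group trends, adjusting for clinical site and cohort". If not, non-parametric tests replace it, "including Wilcoxon signed-rank tests for within-group comparisons", alongside a "Mann-Whitney U test for between-group comparisons". The section calls the work exploratory: "As this is a feasibility study, there is no formal plan for statistical analysis". It adds that an analysis plan developed for a future trial will be run here to see whether it is suitable.

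Table 1 (Inclusion criteria) makes the same instruments part of eligibility. Vestibular and long covid participants need "DHI score >34 AND/OR FGA score <22/30". Stroke and MCI participants need an FGA below 22 and/or a fall in the past 12 months; DHI is not a criterion for them.

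Table 2 marks FGA and DHI at Screening and at week 10, with no mark under Baseline. EQ-5D-5L, ABC and Mini-BESTest, by contrast, are marked at Baseline.

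**The concern.** On the Table 2 schedule, the reading that can admit a participant is also the pre-treatment value in the within-arm comparison. People admitted on a low FGA or a high DHI were partly admitted on measurement error, so their next reading tends toward normal even if nothing has worked. A test of no change within an arm is then tilted toward improvement in the intervention arms and the control arm alike.

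This matters even in a feasibility trial. The Trial design section uses trends for effectiveness to judge whether a future trial is warranted, and to supply its sample size estimates. FGA is one of the clinical measures listed with the primary outcomes. Because the plan is itself being tried out for a definitive trial, the flaw could carry over to a setting where larger arms would raise the false-positive rate.

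**Working it through.** **Figure to reproduce.** None. The protocol gives no power calculation and no error rate for these tests. As arithmetic only, 460/5 = 92 per site, inside the stated 60-100.

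**Inputs from the protocol**
- FGA minimal detectable change (MDC): 4.2 in stroke, 6 in vestibular disorders (Primary outcome measures). DHI MDC: 17.18 (Secondary outcome measures).
- SEM = MDC/(1.96 × √2), taking the MDC as a 95% limit. This gives 4.2 → 1.52, 6 → 2.16 and 17.18 → 6.20.
- Entry rules as in Table 1.

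**Assumptions, because the protocol does not give them**
- Two-sided 5% level, inferred from "Continuous secondary outcome measures will be reported as means with 95% CIs".
- Allocation 1:1, then 1:1 within the intervention group: 460/2 = 230 control, 230/2 = 115 in each technology arm.
- Equal cohort mix. Source FGA mean 18-24, SD 4-5. Share of fallers 30-80%, independent of FGA. Source DHI mean 35-55, SD 20, in the vestibular and long covid cohorts. FGA-DHI correlation -0.3.

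**Method.** Each score is a true value plus independent error, rounded and clipped to the scale. Eligibility is applied to the first reading, with no true change. Week 10 is compared with that reading by a Wilcoxon signed-rank test, 600-1,500 replicates per setting.

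**FGA, whole arm, actual and/or rules** (two-sided rejection rate)

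| Scenario (stroke/MCI mean FGA; fallers; vestibular/long covid mean FGA; mean DHI) | Mean shift | n=115 | n=230 |
|---|---|---|---|
| Mild (18; 80%; 20; 55) | +0.06 | 6% | 6% |
| Middle (20; 50%; 22; 45) | +0.13 | 9% | 13% |
| Strong (22; 30%; 22; 40) | +0.22 | 15% | 23% |
| Extreme (24; 30%; 24; 35) | +0.24 | 18% | 28% |

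Across separate runs the mild case lay at about 5-6%. At n=40 the rates were 6-9%.

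**Hand check of the extreme row.** The SD of change is MDC/1.96, which is 2.14 and 3.06. Pooled over equal halves it is √((2.14² + 3.06²)/2) = 2.64. At n=230, 0.24 × √230/2.64 = 1.38, and Φ(1.38 - 1.96) = Φ(-0.58) = 0.28. At n=115 the same steps give 0.97 and Φ(-0.99) = 0.16, close to the simulated 18%.

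**DHI.** Whole arm: shift -0.14 to -0.28 points, rejection 5-7% at n=115 and n=230. Vestibular and long covid participants alone: shift -0.24 to -0.85, rejection 6-17% at n=115.

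**What moves the FGA rate**
- *Other routes of entry.* In a simpler single-population model (FGA mean 20-24, SD 5, n=230), the rate is 19-59% if 30% can enter without a low FGA, 12-26% if 50% can, and about 6-13% if 70% can. If FGA below 22 were the only route, with stroke/MCI mean 20 and vestibular/long covid mean 22, the shift is 0.57 and the rate 60% at n=115 and 90% at n=230.
- *Larger fluctuation over ten weeks than the MDCs imply.* With the actual rules, SEM × 1.5 gives 8-32% (n=115) and 6-60% (n=230); SEM × 2 gives 7-55% and 10-85%.

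**Controls.** With a fresh baseline reading not used for selection, the within-arm rate returns to 4-6%. The between-arm Mann-Whitney test on change keeps 3.6-5.2% even with the selected baseline, because randomised arms share the same regression to the mean.

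**The case against.** **The inflation may be small.** Every cohort has a second route of entry, and the mild scenario sits at the nominal level. A reader might infer that every arm will show improvement far more often than 5%. The documents do not support that. Rates of 60-90% at the MDC-based error need FGA below 22 to be the only route, which no cohort has. Using the 30% annual fall rate from the Introduction for the other route would borrow a general figure for people over 65. It does not describe these cohorts, nor the DHI route. The bias points the same way in each arm, but all three arms reaching significance together is rare: about 0.4% or less in the mild to strong scenarios. This objection stands and limits the claim.

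**It cannot reach the MCID.** The Discussion reads the predecessor study within its intervention arm, "with FGA and Mini-BESTest findings meeting or approaching the MCID in the intervention group", and a reader might infer that regression to the mean could produce such a gain here. It could not on its own: tenths of an FGA point against 4, and less than one DHI point against 18. That sentence also describes another study and sets no decision rule for this one. This too stands.

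**The analysis is exploratory and a between-arm comparison is planned.** True, and the stated aims compare with standard care. Still, the within-group tests are stated, and trends feed the decision on a future trial.

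**There may be a separate baseline reading.** Recruitment describes eligibility screening by telephone, and Outcome measures has the blinded assessor collect outcome data at baseline; neither matches Table 2. For DHI a second reading is possible. For FGA there is little room: a walking test cannot be done by telephone, and only two site sessions are described. The point is unsettled in the text and needs reconciling.

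**Conclusion.** The concern holds in a limited form. As scheduled in Table 2, the planned within-arm analyses of FGA and DHI are biased toward improvement when nothing has worked, and their false-positive rate can exceed 5%. The protocol does not allow the excess to be bounded, because source means, SDs and the share entering by other routes are not given. Under the entry rules as written, with measurement error from the protocol's MDCs and the assumed source distributions, the FGA rate is about 5-28% and whole-arm DHI about 5-7%. The FGA rate would be higher if few participants entered by another route, or if scores fluctuate more than the MDCs imply. The harm is to within-arm p-values and trend claims. The randomised between-arm comparison is sound on this point. The change is worth making because it is nearly free.

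**What to change.** In the Statistical analysis section, delete the within-group significance tests: the Wilcoxon signed-rank tests and the within-group part of the ANOVA. Report each arm's pre and post means descriptively. State that every conclusion on effectiveness, including the Trial design decision on a future trial and any comparison with an MCID, rests on the between-arm difference with its 95% CI.

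Reconcile Table 2 with Recruitment and Outcome measures, so that it is clear when the pre-treatment FGA and DHI are taken and whether the qualifying reading is also the analysis baseline.

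The cost is a change of wording. No data, visits or participants are affected; only the within-arm p-values are lost.

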## Methods

### Trial design

The study is a multicentre, assessor-blinded RCT, investigating the feasibility and acceptability of the TeleRehaB DSS in persons with stroke, MCI, vestibular dysfunction or long covid.^49^ All participants will be enrolled in a 9-week MBR home exercise programme (HEP), including individualised balance exercises (sitting, standing, walking), cognitive training and exergames (figure 1). All participants will be randomised into one of three study arms, where they will receive a HEP provided under the supervision of a clinician (physiotherapist or sports scientist): (1) the high-technology TeleRehaB DSS group (HT-IG), (2) the low-technology TeleRehaB DSS group (LT-IG) or (3) the control group (CG) standard of care HEP. No matter the study arm allocated, all participants will receive the same prescription pattern, receiving a weekly check-in call by a member of the research team, and remote programme reviews at weeks 3 and 6 by the treating clinician, to discuss exercise modifications, symptoms, falls and any technical problems.

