**Figure 1 F1:**
[figure not shown]
Screenshots of (**A**) physiotherapist avatar and (**B**) representative exergame from the TeleRehab DSS. TeleRehab DSS, TeleRehabilitation Decision Support System.

Exercise data will be collected automatically in TeleRehaB DSS dashboard for the HT-IG and LT-IG, whereas CG participants will be required to log their exercise data manually in a diary provided. Exercises will be prescribed and progressed according to participant feedback and task performance, as assessed by the treating clinician. All treating clinicians will receive appropriate training prior to trial onset.

This study will compare acceptability of the TeleRehaB DSS programme (adherence, recruitment and dropouts) compared with current standard of care (OTAGO or Balance Retraining Booklet), which are commonly used in balance and vestibular rehabilitation. This study will also explore trends for effectiveness across several validated clinical outcome measures to identify whether a future trial is warranted and if so, to provide sample size estimates. The protocol has been developed using the Standard Protocol Items: Recommendations for Interventional Trials reporting guidelines^50^ and the flow of participants through the trial will be recorded in compliance with the Consolidated Standards of Reporting Trials statement^51^ (figure 2).

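### A normality check on the outcome variables chooses the analysis, and for bounded scales it would probably replace a site- and cohort-adjusted model with unadjusted rank tests that name no effect estimate

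*Protocol article*

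**What the plan says.** The Statistical analysis section of the protocol article sets a two-branch rule.

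- The gate: "Normality of outcome variables will be assessed by visual inspection and appropriate statistical tests".
- If it is passed: "intention-to-treat analyses will be conducted using repeated-measures general linear model analysis of variance to explore between-group and within-group trends", "adjusting for clinical site and cohort".
- If it is failed: Wilcoxon signed-rank tests within groups, "Mann-Whitney U test for between-group comparisons and Friedman tests for repeated measures where appropriate". No stratified or adjusted version and no effect estimator is named.

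The same section reports continuous secondary outcomes as means with 95% CIs. It says there is no formal analysis plan for this feasibility study, but that the plan meant for a future trial will be run here to see whether it is suitable.

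Other relevant places:

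- Trial design: "All participants will be randomised into one of three study arms". Its closing part says clinical outcomes are explored "to identify whether a future trial is warranted and if so, to provide sample size estimates".
- Primary outcome measures lists, with feasibility, acceptability, usability and safety, the "clinical measures of Functional Gait Assessment (FGA) and EuroQol five-dimensional descriptive system (EQ-5D-5L) instrument pre-intervention and post-intervention".
- Outcome measures schedules two assessor sessions, at weeks 0 and 10.
- The section on the statistical approach for QALYs and cost-effectiveness gives QALYs and costs a mixed-effects regression adjusted for age, baseline health and site, with no normality gate.

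**The concern.** A linear model with arm, site and cohort makes its distributional assumption about residuals. The gate looks at the raw outcome, which here is pooled over four diagnoses and five sites. The FGA is capped at 30, and Table 1 partly selects participants on a score below 22. EQ-5D-5L utilities use country-specific tariffs, so site differences are built into the raw values. These features can make the raw distribution non-normal even when the model would be adequate.

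Three things follow.

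1. Adjustment for site and cohort disappears when the gate fails. Cohort matters here because the control programme differs by cohort: OTAGO for stroke and MCI, the booklet for vestibular dysfunction and long COVID.
2. No between-group estimate is named in the rank branch, although the trial is meant to inform the size of a future one.
3. Different outcomes can end up with different analyses. Sample size alone can cause this: the Fatigue Severity Scale is given only to the long COVID cohort, so a similar shape might pass there and fail in the full sample.

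**Working it through.** **The plan's own figure.** The article gives 460 as a feasibility convention, with no alpha, power, effect or SD, so there is no power calculation to reproduce. The counts fit: 5 × 60 to 5 × 100 = 300 to 500; 460/5 = 92 per site, or 46 per group per site, within the stated 30–50. All distributional inputs below are assumptions.

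**Step 1. How often would a formal test reject?** Shapiro-Wilk at 5%, with FGA simulated as a rounded normal score capped at 30 (mean 20–24, SD 4.5–5) and EQ-5D utility as a skewed variable capped at 1:

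| n | FGA rejected | EQ-5D rejected |
|---|---|---|
| 92 | 13–96% | 100% |
| 230 | 74–100% | 100% |
| 460 | 100% | 100% |

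With site and cohort shifts added at n = 460, the FGA rejection rate was also 100%. The n = 92 row shows how far the branch depends on sample size.

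**Step 2. Does the gate protect against anything?** With no true difference, an FGA simulation at n = 460 (correlation 0.7, site and cohort effects) gave these rejection rates: Mann-Whitney on week-10 scores 0.055, Mann-Whitney on change 0.045, baseline-adjusted linear model (ANCOVA) with robust SE 0.053. Normality was rejected in every run, yet all three stay near 5%.

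**Step 3. What does the gate cost in power?** The fair comparison is the plan's rank branch against its own parametric branch. With two time points, that branch amounts to an adjusted group-by-time contrast.

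- Simulations 1 and 2: 184 per group (n = 368, which is 80% of 460), 0–30 score, SD about 5, effect 1.5 points, modest site and cohort shifts.
- Closed form: 230 per group, difference d = 0.25 SD, two-sided 0.05. Power ≈ Φ(d√(n/2)/√v − 1.96), where v is 1 for week-10 scores, 2(1 − ρ) for change and 1 − ρ² for ANCOVA. For Mann-Whitney, n is multiplied by 0.955. Site and cohort are ignored, so the change score stands in for the group-by-time contrast.

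Example at ρ = 0.5: Mann-Whitney on week-10 scores, 0.25 × √(219.65/2) − 1.96 = 0.66, power 0.745. Change, 0.25 × √115 − 1.96 = 0.72, power 0.765.

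| Power at ρ = 0.5 / 0.7 | Simulation 1 | Simulation 2 | Closed form |
|---|---|---|---|
| Mann-Whitney, week 10 | 0.76 / 0.76 | 0.76 / 0.75 | 0.745 / 0.745 |
| Mann-Whitney, change | 0.77 / 0.94 | 0.79 / 0.94 | not computed |
| Plan's group-by-time contrast | 0.79 / 0.94 | 0.81 / 0.95 | 0.765 / 0.933 |
| ANCOVA | 0.90 / 0.97 | 0.89 / 0.98 | 0.872 / 0.964 |

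Differences read from the table:

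- Gate, change scores ranked: 0.02 / 0.00 and 0.02 / 0.01, so about 1 point.
- Gate, week-10 scores ranked: 0.03 / 0.18, 0.05 / 0.20 and 0.020 / 0.188, so about 2 to 20 points.
- ANCOVA over the plan's parametric branch: 0.11 / 0.03, 0.08 / 0.03 and 0.107 / 0.031, so about 3 to 11 points.

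The article does not say whether change or week-10 scores would be ranked.

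**The case against.** The best defence is that this is an exploratory feasibility study, declared not powered for effectiveness, and that details may sit in an analysis plan not shown. That lowers the severity. It does not remove the point, because the article states a decision rule that a later plan would have to reverse, and says the analysis itself is on trial here. Visual inspection means rejection by a formal test need not settle the branch, but that leaves a choice made after seeing the data.

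Several stronger readings are tempting, and the article does not support them:

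- *A promised baseline adjustment is lost.* Only site and cohort are named. Baseline enters as a time level of the repeated-measures model, and ranking change scores would keep much of that.
- *EQ-5D-5L loses its adjusted analysis altogether.* Only the raw score is exposed; QALYs keep their own adjusted, ungated model.
- *No means or SDs will be available.* Continuous secondary outcomes get means with 95% CIs whichever test is used, and an SD can be recovered from the interval and n. That sentence does not literally cover FGA and EQ-5D-5L, and no adjusted difference is promised for any outcome in the rank branch.
- *Mann-Whitney cannot serve three arms.* It can compare pooled intervention with control, and high-tech with low-tech, which fits the second randomisation within the intervention group.
- *Friedman is applied to two time points.* It is qualified as for use where appropriate, and weekly and monthly diaries supply more repeats.
- *The rank tests are invalid, or the gate costs the full gap between Mann-Whitney and ANCOVA.* Type I error holds, and ANCOVA is not in the plan. At ρ = 0.5 in simulation 1 the gap is 0.90 − 0.76 = 0.14, of which 0.11 comes from preferring ANCOVA to the plan's own model.

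**Conclusion.** The point holds, at moderate severity, as an improvement that costs nothing in data. The gate examines the wrong quantity. For FGA and the raw EQ-5D-5L score at the planned N it would very likely select rank tests if a formal test decides. Those tests drop the site and cohort adjustment, name no between-group estimate and allow analyses to differ between outcomes. The main harm is to the stated purpose of trying out an analysis and providing inputs for a future trial's size.

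The power cost is secondary and depends on an unstated choice: about 1 point if change scores are ranked, about 2 to 20 if week-10 scores are ranked. Moving to a baseline-adjusted model would add a further 3 to 11 points over the plan's parametric branch. All these figures rest on assumed distributions, effects and correlations of 0.5–0.7. They show relative performance and do not predict this trial's power.

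**What to change.** Remove the normality gate. For each continuous outcome, prespecify one linear model of the week-10 value on arm, baseline value, site and cohort, reporting the adjusted difference with a 95% CI. Check residuals, and if they are badly skewed keep the model and use robust or bootstrap intervals. Report pooled TeleRehaB versus control, and high-tech versus low-tech, as named contrasts from that model. State explicitly that FGA and EQ-5D-5L are included. Keep Wilcoxon, Mann-Whitney and Friedman tests, if wanted, as sensitivity analyses only. Leave the QALY and cost model as it is.

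The cost is wording in the protocol and analysis plan, with no new data, visits or participants.
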